**Incidence of all cardiovascular events ****1260 per 100,000**

#### Clinical significance

We aim to demonstrate at least a 10% reduction in the cardiovascular event rate. This means that for a positive outcome, the event rate in the intervention population must be ≤90% of the event rate in the control population. We therefore estimated the necessary sample size for this reduction to be detected at the 5% level with 80% power.

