### Primary outcome

Difference in the annual incidence rate of cardiovascular events (see definition in the appendix) in the intervention and control populations during the two years of the study, and for a third year following the end of the e-Nudge intervention.

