#### Estimating population size needed

A Poisson distribution model is appropriate for events that are rare on an individual level, occurring randomly and independently at a constant rate in a population [37].

Assuming a Poisson distribution, the formula for the sample size is:

where:

λ_0 _= the expected incidence of cardiovascular events (i.e. 1260/100,000)

δ = new incidence in the intervention group

*z*_1-*α *_= standardised normal distribution value based on 0.05 significance level

*z*_1-*β *_= standardised normal distribution values for 80% power

*N *= total number of patients required in the study

*Nw *= total number of patients required in the study + 10% to account for practice withdrawal

For 80% power and 0.05 significance level (2-tailed) [38] (see Table 1):

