**Table 1 T1:** 

Reduction in incidence (%)	*z*_1-*α*_	*z*_1-*β*_	λ_0_	δ	N	Nw
10	1.96	0.8416	0.0126	0.001260	64133.46	70546.80

The practice population required to detect both statistically and clinically significant changes in the cardiovascular event rate is therefore estimated to be approximately **70,000**, the combined list size of all age groups in participating practices.

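### The protocol's condition for a positive outcome (rate ratio of 0.90 or less) equals the effect assumed for power, so the stated 80% does not apply to it; at a true 10% reduction the chance of meeting it is about 50%

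*Protocol article*

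**What the plan says.** Under Clinical significance, within the sample size calculation, the protocol article makes three linked statements:

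- The aim: "We aim to demonstrate at least a 10% reduction in the cardiovascular event rate".
- What that means for success: "for a positive outcome, the event rate in the intervention population must be ≤90% of the event rate in the control population".
- The sizing: "We therefore estimated the necessary sample size for this reduction to be detected at the 5% level with 80% power".

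Under Estimating population size needed, the test is two-sided at 5% ("For 80% power and 0.05 significance level (2-tailed"). Table 1 uses a 10% reduction, with λ0 = 0.0126 and δ = 0.001260, and gives N = 64133.46, or 70546.80 after adding 10% for practice withdrawal. The text after Table 1 describes the resulting figure of about 70,000 as "The practice population required to detect both statistically and clinically significant changes in the cardiovascular event rate".

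The Primary outcome section names a difference in annual incidence rate, "during the two years of the study, and for a third year following the end of the e-Nudge intervention", and gives no threshold. The Statistical analysis section gives the software, the intention-to-treat basis and the reporting guideline. The sentence under Clinical significance is therefore the only place in the article that says what a positive outcome is.

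**The concern.** A power calculation against no difference asks how often the trial rejects a ratio of 1 when the true ratio is 0.90. The stated success condition asks how often the rate ratio comes out at 0.90 or below. These are different events with different probabilities, and the protocol attaches its power figure to the first while defining success by the second.

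If the true ratio equals the pass mark, the estimate is centred on the pass mark. A larger trial narrows the spread around 0.90 but does not move the centre, so the chance of landing on the favourable side stays near one half.

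At stake is how the result will be called. A statistically significant reduction of less than 10% would answer the primary research question (can the system reduce incidence?) with yes, yet fail the stated condition. Unless this is settled before outcome data are seen, such a result could be labelled positive or negative after the fact.

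**Working it through.** **Inputs from the protocol.** λ0 = 0.0126; assumed ratio 0.90; z = 1.96 and 0.8416; N = 64133.46 in total before the withdrawal allowance and about 70,000 after it; two years of intervention plus a third year of outcome data.

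**Assumptions of this check.** Allocation is 1:1 (the ratio is not stated). The 0.0126 rate is applied to the whole sample, as Table 1 does, giving 32,067 per arm (64133.46 / 2) or 35,000 per arm (70,000 / 2). The effect is constant over the years counted.

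**1. Reproduce the plan's figure.** The formula itself is not legible in the text available, but one form matches Table 1 exactly:

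N = [(1.96·√λ0 + 0.8416·√(λ0 + δ)) / δ]² = [(0.22001 + 0.09908) / 0.00126]² = 64133.46

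64133.46 × 1.10 = 70546.81, agreeing with Table 1 apart from the last digit. This is a one-sample test against no difference. It has no term for the 90% condition.

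**2. Chance of an observed ratio of 0.90 or less when the true ratio is 0.90** (exact Poisson, equal person-time):

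| Per arm | Years | Expected events, control / intervention | Chance of meeting the condition |
|---|---|---|---|
| 32,067 | 1 | 404 / 364 | 50.1% |
| 35,000 | 1 | 441 / 397 | 50.1% |
| 35,000 | 2 | 882 / 794 | 50.07% |
| 35,000 | 3 | 1323 / 1191 | 50.06% |
| 1,000,000 | 1 | 12,600 / 11,340 | 50.02% |
| 10,000,000 | 1 | 126,000 / 113,400 | 50.01% |

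The small excess over 50% comes from the skewness of Poisson counts. If significance is required as well, the joint chance is 31% to 33% with one year of data and still about 50% with two or three years.

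**3. True reduction needed for an 80% chance of meeting the condition.** With SE = √(1/events in control + 1/events in intervention), the true ratio is approximately exp(ln 0.90 − 0.8416·SE). Events are those expected at a ratio of 0.90.

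- One year: SE 0.069 to 0.072, ratio about 0.847 to 0.849, reduction about 15%.
- Two years: SE 0.049 to 0.051, ratio about 0.862 to 0.864, reduction about 14%.
- Three years: SE 0.040 to 0.042, ratio about 0.869 to 0.870, reduction about 13%.

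**4. Which significant results the condition would reject.** Two-sided 5% significance needs an observed ratio of about exp(−1.96·SE) or less.

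- One year: about 0.87. Every significant reduction already exceeds 10%, so the condition rejects none.
- Two years: 0.905 with 32,067 per arm, 0.909 with 35,000. Significant reductions from about 9.5% (9.1% at the larger size) up to 10% are rejected.
- Three years: 0.922 with 32,067 per arm, 0.925 with 35,000. Significant reductions from about 8% up to 10% are rejected.

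**5. Power of the significance test alone at a true ratio of 0.90**, as Φ(−ln 0.90 / SE − 1.96):

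- One year: 31% to 33%.
- Two years: 54% to 58%.
- Three years: 71% to 75%.

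Dropping the condition therefore does not by itself bring power to 80% at the planned size.

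**The case against.** The strongest reply is that the sentence only names the target difference for planning. It sits inside the sample size section, leads straight into the power statement and does not use the word observed; the outcome and analysis sections contain no 90% rule. On that reading the 50% cap disappears. The reading is possible, but the text says what must hold for a positive outcome, the sentence after Table 1 repeats the joint claim of statistical and clinical significance, and no other criterion is offered. The wording has to be changed for that reading to be the plain one.

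A second reply is that the protocol attaches 80% to detection at the 5% level, not to the 90% condition, and that the aim is a reduction of at least 10%. Both statements are right. A true reduction larger than 10% would meet the condition more often (step 3). But the effect used in Table 1 is exactly 10%, and there the condition is met about half the time.

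Three stronger inferences are tempting and should not be drawn:

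- That demonstrating at least a 10% reduction requires the upper confidence limit to lie below 0.90. The protocol states no confidence-limit criterion, so power figures built on one have no basis in it.
- That any significant reduction of 8% to 9% would be rejected. With two years of data and SE 0.051, an observed 9% reduction gives p of about 0.065 and an 8% reduction about 0.10, so neither is significant. The case arises for this range only with about three years of data.
- That the wording is what keeps the trial from 80% power. At the planned size the shortfall in step 5 remains without the condition, and it comes from the one-sample formula behind Table 1.

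**Conclusion.** The point stands as a contradiction between the stated success condition and the stated power. Read as a rule on the observed rates, the condition is met about 50% of the time at a true ratio of 0.90, and this does not depend on event rate, sample size or length of follow-up. The 80% was computed only for a test against no difference.

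The 13% to 15% and the bands of rejected significant results are illustrations. They rest on 1:1 allocation, on the all-age rate of 0.0126 applied to about 32,000 to 35,000 per arm although only patients over 50 are randomised, and on a constant effect, including in the third year after the intervention stops. Other event counts would shift these figures but not the 50%.

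The practical reach is limited. With one year of data the condition rejects no significant result, and with two years it rejects only a narrow band just under 10%. It is still a rule that the protocol fixes wrongly, not a detail left to an analysis plan.

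**What to change.** Replace the sentence under Clinical significance. State that a positive primary result is a two-sided 95% confidence interval for the rate ratio, intervention to control, that excludes 1 in favour of the intervention. Keep 10% as the effect assumed for planning and as the benchmark against which the estimate and its interval are discussed for clinical importance. Reword the sentence after Table 1 so that the 80% is attached only to the test against no difference.

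If the sponsor prefers to keep the 90% condition, restate the power for it as about 50% at most at a true 10% reduction, or give the larger true reduction for which 80% is claimed.

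The cost is one or two sentences of protocol wording, with no change to randomisation, outcome or data collection. It should be made before outcome data are examined by arm. It does not repair the sample size: the one-sample formula in Table 1 needs its own correction.

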#### Estimating population size needed

A Poisson distribution model is appropriate for events that are rare on an individual level, occurring randomly and independently at a constant rate in a population [37].

Assuming a Poisson distribution, the formula for the sample size is:

where:

λ_0 _= the expected incidence of cardiovascular events (i.e. 1260/100,000)

δ = new incidence in the intervention group

*z*_1-*α *_= standardised normal distribution value based on 0.05 significance level

*z*_1-*β *_= standardised normal distribution values for 80% power

*N *= total number of patients required in the study

*Nw *= total number of patients required in the study + 10% to account for practice withdrawal

For 80% power and 0.05 significance level (2-tailed) [38] (see Table 1):

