### Data quality assurance measures

We will examine the cause of death of every patient in the practices over age 50 years who dies during the study, to ensure that all cardiovascular deaths are recorded appropriately in searchable form prior to outcome data extraction. Any patient recorded as having more than one cardiovascular event during the study will have their clinical record examined, to identify patients who have had the same event recorded twice (which may happen when a consultation for a stroke, TIA or myocardial infarction is mistakenly labelled as a "new episode" rather than a "review"). This process will be carried out both on controls and intervention patients. In addition, we will examine the notes of any patient who has a record of an event dated within 4 months of registration with a practice, in case this event occurred in the past but was incorrectly dated when the patient registered.

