### Sample size calculation

#### Event rates

Our study defines a cardiovascular event as a new diagnosis of CVD, a new myocardial infarction, a new stroke, a new transient ischaemic attack, or sudden death from CVD. A new stroke in someone with a previous stroke will count as a new event. An acute myocardial infarction in a patient previously diagnosed with angina will be recorded as a new event, but a new onset of angina in a patient who already had a diagnosis of acute myocardial infarction might not be recorded as a new diagnosis, as the patient will already be on the CHD register.

The British Heart Foundation [35] has compiled an estimate of the number of cardiac events in the UK population in 2002 from several available data sources. The number of myocardial infarctions (all ages) was estimated to be 268,000, while the number of new cases of angina (all ages) was estimated to be 338,000

The UK population was 59,321,700 in 2002 [Sources: Office for National Statistics, General Register Office for Scotland, Northern Ireland Statistics and Research Agency], so estimated incidence rates *for coronary heart disease *are

**Incidence of myocardial infarction **451.77 per 100,000

**Incidence of new case of angina **569.77 per 100,000

For *cerebrovascular disease*, the OXVASC study [36] provides a local source of information drawn from an Oxfordshire population. The incidence rates were:

**Incidence of stroke **187 per 100,000

**Incidence of TIA **51 per 100,000

Therefore

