2. A new stroke or transient ischaemic attack (TIA) (whether or not already on the Stroke register)

3. A new myocardial infarction (whether or not already on the CHD register).

4. Sudden death from cardiovascular disease.

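### The primary outcome counts repeat events in the same patient, but the sample size assumes independent Poisson events and allows nothing for within-patient dependence

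*Protocol article*

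**What the plan says.** The Primary outcome section compares annual incidence rates of cardiovascular events between the arms. Nothing limits a patient to a first event. Under Event rates: "A new stroke in someone with a previous stroke will count as a new event". Definition 5d in the appendix does the same for infarction, "A new myocardial infarction (whether or not already on the CHD register", and for stroke and TIA.

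The section on data quality assurance expects several events per patient: "Any patient recorded as having more than one cardiovascular event during the study will have their clinical record examined". The stated purpose is to find one event entered twice. Genuine recurrences are not said to be removed.

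The sample size section adopts a Poisson model, described as suitable for rare events "occurring randomly and independently at a constant rate in a population". Its inputs are "the expected incidence of cardiovascular events (i.e. 1260/100,000" (per person per year), a 10% reduction, two-sided 5% significance and 80% power. Table 1 gives N = 64133.46, or 70546.80 with 10% added for practice withdrawal.

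The Outcome analysis and Statistical analysis sections give the software, intention to treat and CONSORT. They name no model or variance estimator for the primary comparison.

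**The concern.** The outcome definition and the distributional assumption do not fit together. An infarction after angina, a stroke after a TIA or a second stroke all give a further event in a patient who already has one. Angina and infarction alone make up 569.77 + 451.77 = 1021.54 of the 1259.54 expected events per 100,000 (81%), so the angina-then-infarction route is not marginal. Data are collected for three years, which leaves time for recurrence.

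If repeats are more common than independence implies, the event count has a larger variance than the Poisson model gives. A sample size built on the Poisson variance then has less power than stated. If the same variance were used in the analysis, the interval for the rate comparison would be too narrow. The target effect is only a 10% reduction, so a modest error in the standard error could change the conclusion.

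**Working it through.** **1. Reproduce the stated N.** The formula itself is not legible in the text. The one-sample Poisson form reproduces the table:

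N = (z_a·√λ0 + z_b·√(λ0 + δ))² / δ², with z_a = 1.96, z_b = 0.8416, λ0 = 0.0126, δ = 0.00126 (Table 1).

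N = (1.96 × 0.11225 + 0.8416 × 0.11773)² / 0.00126² = (0.22001 + 0.09908)² / 0.00126² = 64,133.46. Times 1.10 this is 70,546.80.

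Both match exactly. The variance per patient-year is the rate itself, with no dispersion factor.

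**2. Variance with repeats.** Let a proportion p of patients have any event, and let a share f of those have exactly two. Then E[Y] = p(1 + f) and E[Y²] = p(1 − f + 4f) = p(1 + 3f). Ignoring the square of the small mean, the ratio of the variance to the Poisson variance is

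φ = (1 + 3f)/(1 + f).

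The documents give no value for f, so a range is assumed.

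**3. Consequences.**
- Type I error of a two-sided 5% test that uses the Poisson variance: 2·(1 − Φ(1.96/√φ)).
- N for 80% power: 64,133 × φ.
- Power at N = 64,133 with a valid variance: Φ((δ√(N/φ) − z_a√λ0)/√(λ0 + δ)).

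| f (assumed) | φ | True SE / Poisson SE | Type I error, Poisson variance | Power, valid variance | N needed (before +10%) |
|---|---|---|---|---|---|
| 2% | 1.04 | 1.02 | 5.4% | 78.5% | 66,648 |
| 5% | 1.10 | 1.05 | 6.1% | 76.5% | 70,241 |
| 10% | 1.18 | 1.09 | 7.1% | 73.4% | 75,794 |
| 20% | 1.33 | 1.15 | 9.0% | 68.4% | 85,511 |

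**4. Accuracy of the approximation.** The exact ratio is φ minus the mean count per patient. On the plan's rate that mean is 0.0126 over one year and 3 × 0.0126 = 0.0378 over three. Over three years, f = 2% gives 1.039 − 0.038 = 1.001, which is no excess at all: independent events at that rate would themselves give about 1.9% of event patients a second event. For f = 20% the ratio is 1.333 − 0.038 = 1.296. The table is therefore slightly pessimistic, most noticeably in its first row.

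**5. Simulation.** With 35,000 patients per arm, a mean of 0.0378 events per patient and 20,000 replicates, the test with Poisson variance rejected a true null in 5.6%, 7.0% and 8.8% of trials for f = 5%, 10% and 20%. With a patient-level robust variance the figures were 4.6%, 5.0% and 4.8%.

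**The case against.** A reader might infer that the trial's primary test will have a type I error above 5%. The documents do not support that. The Poisson statement justifies a sample size formula, and the analysis sections fix no model. A robust or overdispersed analysis is compatible with everything written, and it may be specified in an analysis plan that is not shown. The 5.4% to 9.0% figures are therefore conditional.

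A reader might also infer that a first infarction scores twice, once as entry to the CHD register and once as an infarction. Read naturally, the items of definition 5d are alternative ways to qualify, and the record check on patients with more than one event would largely catch such a case. What remains is only that definition 5d does not itself say that one episode counts once.

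Three further objections stand. The repeat share is unknown, and at the low end the effect is negligible. Differences in risk between patients add no extra variance by themselves; they act only through repeats. Replacing the primary outcome by first events would be a change of outcome, not of wording: it would discard f/(1 + f) of events, which is 9% at f = 10% and 17% at f = 20%, in a trial that explicitly targets patients with established disease.

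None of this removes the mismatch between the outcome as defined and the assumption behind N. The loss of power follows for any valid analysis of all events if repeats exceed what independence implies.

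**Conclusion.** The point holds as one about the sample size assumption and, conditionally, about the analysis. The protocol counts all events and keeps genuine repeats, while its sample size sets the variance equal to the mean. For assumed repeat shares of 2% to 20% the variance is about 1.04 to 1.33 times Poisson, and somewhat less if counts are accumulated over three years. Under the protocol's own formula, power with a valid variance is about 76% to 68% for shares of 5% to 20%, against the stated 80%. Inflated type I error is a risk to close off, not a stated feature of the plan.

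The power figures take the protocol's one-sample formula as given. Whether that formula suits a two-arm comparison is a separate question; these figures show only the change due to repeats.

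**What to change.** - Keep the all-events primary outcome.
- State that the arms' rates will be compared with a variance robust to clustering on patient, or with an overdispersed model such as negative binomial.
- Add to definition 5d that one clinical episode counts once across its items 1 to 4.
- In the sample size section, state that the independence assumption and the 80% power make no allowance for repeat events, and give the power for a plausible range of repeat shares.
- If wanted, add first event per patient as a sensitivity analysis, not as a replacement for the primary outcome.

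The cost is a few sentences, slightly wider intervals and a less favourable stated power. No extra data are needed, because patients with more than one event are already to be identified and their records checked. The wording should be settled before outcome data are examined, so that the choice of count and variance cannot depend on the results.

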**Table 1 T1:** 

Reduction in incidence (%)	*z*_1-*α*_	*z*_1-*β*_	λ_0_	δ	N	Nw
10	1.96	0.8416	0.0126	0.001260	64133.46	70546.80

The practice population required to detect both statistically and clinically significant changes in the cardiovascular event rate is therefore estimated to be approximately **70,000**, the combined list size of all age groups in participating practices.

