### 1. Justification for the thresholds and search protocols used in the study

#### a) Age group

We decided to include in the searches only those patients over 50 yrs, as the prevalence of cardiovascular disease begins to climb steeply at this age [35]. As the main outcome involves a comparison of the effect of the intervention on event rates, this will avoid the dilution of each denominator population by low risk patients.

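### The sample size comes from a one-sample Poisson formula, so the two-arm trial has about 54% power over its two intervention years, not the stated 80%

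*Protocol article*

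**What the plan says.** Under Clinical significance, the aim is a reduction of at least 10%: "the event rate in the intervention population must be ≤90% of the event rate in the control population". The section continues: "We therefore estimated the necessary sample size for this reduction to be detected at the 5% level with 80% power". The next section, Estimating population size needed, makes the test two-tailed.

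That section defines λ0 as the expected incidence, 1260 per 100,000. It defines δ as the "new incidence in the intervention group" and N as the "total number of patients required in the study". Nw is N plus 10% for practice withdrawal. No term is listed for a second arm, an allocation ratio or length of follow-up.

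Table 1 gives z values of 1.96 and 0.8416, λ0 = 0.0126, δ = 0.001260, N = 64133.46 and Nw = 70546.80. The text below it concludes: "The practice population required to detect both statistically and clinically significant changes in the cardiovascular event rate is therefore estimated to be approximately" 70,000, and describes this as "the combined list size of all age groups in participating practices".

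Elsewhere, the Randomisation section allocates patients over 50 to two groups. The Primary outcome section compares the two groups' annual incidence over two years, and for a third year after the intervention ends. Appendix 1a says the plan is to "include in the searches only those patients over 50 yrs".

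**The concern.** The control rate will be estimated from concurrent randomised patients, so it carries sampling error of its own. A formula that takes the control rate as known leaves that error out. If its result is then treated as the total for both arms, the shortfall is compounded: each arm gets half of a figure that was already too small for one arm.

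The recruitment target rests on 80% power for a 10% reduction. If true power is well below that, a neutral result could be read as evidence against the e-Nudge from an adequately powered trial, when the trial had a large chance of missing the effect it was designed to find.

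**Working it through.** **Inputs, all from the Sample size calculation section.** λ0 = 0.0126 per person-year (451.77 + 569.77 + 187 + 51 = 1259.54 per 100,000, rounded to 1260). A 10% reduction gives λ1 = 0.01134 and a difference of 0.00126. The z values are 1.96 and 0.8416. Assumed here: 1:1 allocation, a constant event rate, and the full effect throughout follow-up.

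**1. Reproducing Table 1.** The equation itself is missing from the text at hand, but its inputs and outputs are printed. The one-sample Poisson formula gives

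N = [1.96·√0.0126 + 0.8416·√(0.0126 + 0.00126)]² / 0.00126² = 64,133.46

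and 64,133.46 × 1.1 = 70,546.80. Both agree with Table 1 to the last decimal. Two details follow:

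- The match needs λ0 + δ, a 10% increase. With λ0 − δ, the planned reduction, the result is 60,388.
- δ enters as the difference, 0.00126. The new incidence, which is how the text labels it, would be 0.01134.

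**2. The two-arm requirement.**

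Person-years per arm = (1.96 + 0.8416)² × (0.0126 + 0.01134) / 0.00126² = 118,357

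The total is 236,715 person-years, or about 236,715 × 0.01197 ≈ 2,830 events. Log-rate and square-root versions give totals of 236,934 and 236,551, so the choice of two-sample method does not matter. The ratio to the stated N is 236,715 / 64,133 = 3.7. In patients, before any withdrawal allowance, this is 118,357 followed for two years or 78,905 followed for three.

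**3. Power at the stated target.** With m person-years per arm,

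power = Φ(0.00126 / √(0.02394 / m) − 1.96)

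| Follow-up | m (N = 64,133 in total) | Power | Power with all 70,547 retained | Reduction detectable with 80% power (N = 64,133) |
|---|---|---|---|---|
| 1 year | 32,067 | 31% | 33% | 18.8% |
| 2 years | 64,133 | 54% | 58% | 13.5% |
| 3 years | 96,200 | 71% | 75% | 11.1% |

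**4. Age mismatch.** N is an all-age list multiplied by an all-age rate, but only over-50s are randomised. The powers above therefore assume that every event falls in over-50s. The document gives no share. If 10% of events fell below that age (assumption), power would be 28%, 50% and 67% over one, two and three years. For shares of 5% to 20% under 50, two-year power is 52% to 45%.

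**The case against.** The 54% figure is conditional, and several points could move it.

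- **Third year.** The primary outcome also covers a third year, which raises power to 71%, or 75% with no withdrawals. That year follows the end of the intervention, so this assumes the effect persists in full. It still falls short of 80%.
- **Withdrawals.** Practices that withdraw are censored only from that date (Outcome analysis), so they contribute some person-years. A fair two-year range is 54% to 58%.
- **Event rate.** The 1260 figure adds no separate term for sudden cardiovascular death, while some new angina will go uncounted, so the direction of any error is unclear. With the full list over three years, a rate about 12% higher would restore 80%. At two years with 64,133 it would have to be about 85% higher.
- **Recruitment room.** The target is a requirement, not a cap, and up to twenty-six practices may be invited. The two-year requirement plus 10% is 118,357 × 1.1 ≈ 130,200, a mean list of about 5,000 over 26 practices. So 54% is the power at the stated target, not necessarily at the number finally recruited.
- **N per arm.** If N were per arm, two-year power would be 83%. The document defines N as the study total, however, and 70,000 as a combined list size.

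Some of the accompanying slips are minor. Using λ0 + δ makes N about 6% larger, which is conservative. The wrong label for δ changes no number. An all-age rate on an all-age list is a workable way to count events if few occur under 50. Leaving out follow-up time partly offsets the one-sample error. None of this rescues the stated power.

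**Conclusion.** The concern holds. Table 1 applies a one-sample formula to a two-arm comparison and calls the result the study total. At that size, power for a 10% reduction is 54% to 58% over the two intervention years and 71% to 75% if the third year is added with the effect undiminished. At two years with 64,133 people, 46% of such trials would miss a true 10% reduction.

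These figures rest on 1:1 allocation, a constant 1260 per 100,000 per year, the full effect throughout, and all events falling in the randomised over-50s. The last two assumptions are favourable to the trial. The arithmetic in Table 1 is correct for the formula used; the fault lies in the choice of formula. The labelling of δ and N and the sign of δ are secondary, but belong in the same correction.

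**What to change.** In Estimating population size needed:

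1. Replace the formula with person-years per arm = (z_α + z_β)²(λ0 + λ1) / (λ0 − λ1)², where z_α is the two-sided value 1.96.
2. Define δ as the difference λ0 − λ1, a reduction, and state the allocation ratio.
3. State the follow-up that the calculation uses, and whether the third year counts towards the power claim.
4. Give λ0 and N for the over-50s who are randomised, or keep the all-age version and state the assumed share of events in over-50s. Power depends on the expected number of events, so restating rate and N for over-50s changes the result only by the share of events that falls under 50.
5. Keep the 70,000 list and restate what it delivers: about 54% power for a 10% reduction over two years (58% if no practice withdraws), or 80% power for a reduction of about 13.5%.

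The cost is one recalculation and some rewording. The stated power becomes less favourable, and no extra patients are needed. If the investigators want to retain 80% power for a 10% reduction over two years, the corrected target is about 130,200 including the 10% allowance. That would be a separate recruitment decision.
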